### Randomization

Women will be randomized to the two treatment arms (Group A and Group B) using randomly permuted blocks of size 2, 4 or 6 (also randomly chosen) within 6 strata accounting for BMI (30–34.9; and 35–50 kg/m^2^), age (18–29 and 30–38 year-old), and parity (0 or 1+).

#### Group A: Moderate Weight Loss (MWL)

Nutritional advice will be delivered by a qualified dietician in accordance with the ‘Australian Guide to Healthy Eating’. Daily energy expenditure will be calculated based on Basal Metabolic Rate and Activity Level (Harris-Benedict formula). A hypocaloric diet (500 cal deficit from the daily energy expenditure) will be recommended to achieve a weight loss of 0.5 kg per week. A food diary and an ‘Allan Borushek’s Calorie, Fat and Carbohydrate Counter’ book (Hinkler books, 2014) will be provided to participants as tools to assist weight loss. Over 12 weeks, ≤3% of body weight loss is expected. This is current best practice.

#### Group B: Substantial Weight Loss (SWL)

Women will be instructed to replace two meals per day with a commercially available very low energy dietary formulation, Optifast **®** (Nestle Nutrition, Australia). The third meal of the day must consist of 150 g of protein (meat, chicken, fish, tofu, eggs), 2 cups of low-starch vegetables and salad dressed with 2 tablespoons of oil (to stimulate the gallbladder and prevent gallstones). Nutritional advice will be delivered by a qualified dietician. The group will receive ‘Allan Borushek’s Calorie, Fat and Carbohydrate Counter’ book (Hinkler books, 2014) but will be advised that the information in this book will only be relevant after completion of the intervention phase. Total daily calorie intake is approximately 800 cal. Over 12 weeks, 10–15% total body weight loss is expected [33] (Table 1).

**Table 1 Tab1:** Sample constituents of the VLED product

OPTIFAST® VLCD Shake Vanilla 53 g			
Servings per pack: 12 Serving Size: 53 g (Powder)	Average quantity per serving	Average quantity per 100 g	Ave quantity per 100 mL (made up with 200 mL water)
Energy	840 kJ	1580 kJ	354 kJ
	201 Cal	379 Cal	85 Cal
Protein	20 g	37.7 g	8.4 g
Fat-total	4.5 g	8.5 g	1.9 g
- Saturated	0.9 g	1.7 g	0.4 g
- Linolenic acid	1.2 mg	2.2 mg	0.5 mg
- α-Linolenic acid	196 mg	370 mg	83 mg
Carbohydrate	18.2 g	34.4 g	7.7 g
- Sugars	10.1 g	19 g	4.3 g
- Lactose	9.5 g	18 g	4.0 g
Dietary fiber	3.6 g	6.8 g	1.5 g
Sodium	215 mg	410 mg	92 mg
Vitamin A	345 μgRE	650 μgRE	146μgRE
Thiamin (B1)	0.58 mg	1.10 mg	0.2 mg
Riboflavin (B2)	0.74 mg	1.40 mg	0.3 mg
Niacin	8.0 mgNE	15 mgNE	3.4mgNE
Pantothenic acid	2.7 mg	5 mg	1.1 mg
Vitamin B6	1.0 mg	1.9 mg	0.4 mg
Biotin	10.6 μg	20 μg	4.5 μg
Folic acid	110 μg	210 μg	47 μg
Vitamin B12	1.1 μg	2 μg	0.4 μg
Vitamin C	40 mg	76 mg	17 mg
Vitamin D	3.7 μg	7 μg	1.6 μg
Vitamin E	7.4 mgTE	14 mgTE	3.1 mgTE
Vitamin K	31.8 μg	60 μg	13.4 μg
Calcium	420 mg	800 mg	180 mg
Chromium	13 μg	25 μg	5.6 μg
Copper	1.1 mg	2 mg	0.4 mg
Fluoride	340 μg	650 μg	146 μg
Iodine	98 μg	185 μg	42 μg
Iron	8.0 mg	15 mg	3.4 mg
Magnesium	160 mg	300 mg	67 mg
Manganese	0.8 mg	1.5 mg	0.3 mg
Molybdenum	18.6 μg	35 μg	7.8 μg
Phosphorus	360 mg	680 mg	150 mg
Selenium	40 μg	75 μg	16.8 μg
Zinc	4.2 mg	8 mg	1.8 mg
Potassium	955 mg	1800 mg	405 mg
Chloride	280 mg	530 mg	120 mg
Gluten	Nil detected	Nil detected	Nil detected

### Intervention

The trial will involve three phases.

#### Phase 1: Weight loss (Weeks 0–12)

##### Weeks 0 & 12 (all participants)

On arrival to the clinic, a fasting blood sample (20 ml) will be taken for measurement of plasma glucose, insulin, lipid profile (total cholesterol, LDL, HDL, triglycerides, non-esterified fatty acids (NEFA)), leptin and C-reactive protein (CRP)). The specified period of fasting is 8–12 h with blood samples drawn between 08:00 and 10:00 am. A urine and serum pregnancy test will be performed. Urinalysis will be performed for urinary ketones. Maternal anthropometry (weight, waist and hip circumference, skin fold thickness measurement) and blood pressure will be measured (see Data and Biosample collection 1.1 and 1.2).

Participants will be asked to avoid pregnancy using a medically proven form of contraception. Adequate methods of contraception include barrier contraceptives, hormonal contraceptives (oral, implanted, injectable) or mechanical products (intra-uterine device). The patient’s understanding of this will be documented. Standard pre-pregnancy medical advice for obese women planning pregnancy will be discussed. This includes the use of a multi-vitamin containing iodine 150μg (one tablet PO daily) and high dose folate (5 mg PO daily) [53].

The medical doctor will discuss the national guidelines for exercise with the participant using the NHMRC brochure titled “Australia’s Physical Activity and Sedentary Behaviour Guidelines for Adults”. Participants will be provided with a pedometer (Yamax 200S) and will be asked to wear the pedometer for 7 consecutive days (Week 2 of the weight loss phase). An average step count will be recorded. Exercise does not play a significant role in short-term weight loss but we wish to demonstrate that differences in weight loss between the groups are not due to exercise [54, 55].

Participants will be provided with a survey to take home and complete before the next study visit. This survey is based on the previously published Health in Pre-conception, Pregnancy and Post-birth (HIPPP) Study [56]. It is intended to assess areas including depression, anxiety, body image and activity level, which may impact health during pregnancy. This is expected to take around 1 h to complete. The decision to participate or not participate in this aspect of the study will not impact involvement in other aspects of the study.

##### Weeks 2,4,6,8,10

Maternal anthropometry and blood pressure will be measured (see Data and Biosample collection 1.1 and 1.2). A brief medical history will be taken and medication will be adjusted as required. A urine test will be collected. A urine pregnancy test and urinalysis for urinary ketones will be performed. The dietician will provide ongoing dietary counselling.

#### Phase 2: Weight maintenance (Weeks 13–16)

Both study arms will be asked to adopt a healthy balanced diet based on the “Australian Guide to Healthy Eating” for a period of 4 weeks and will be asked to aim for weight maintenance. At week 16, maternal anthropometry and blood pressure will be measured (see Data and Biosample collection 1.1 and 1.2). If greater than 3 kg of weight regain has occurred, participants will see the dietician for further dietary counselling. At the end of this phase, women will be advised contraception can be ceased and they may try to conceive.

#### Phase 3a: Pre-pregnancy (Week 17–60)

Women from both groups will be seen every 3 months whilst attempting to conceive. Maternal anthropometry and blood pressure will be recorded (see Data and Biosample collection 1.1 and 1.2). Any medical issues and changes in medication will be documented. A urine pregnancy test will be performed. Women will see the dietician to assist weight maintenance. If pregnancy has not occurred within 12 months of Phase 1 of the trial, involvement in the trial will cease. If appropriate, the women will be referred on for fertility care.

#### Phase 3b: Pregnancy (Conception-3 days post delivery)

Women will contact the study coordinator when a home pregnancy test is positive. There is no limitation to how pregnancy is achieved (spontaneous pregnancy, clomiphene induction, artificial reproductive technology). Method of conception and approximate estimated date of conception will be recorded. It is accepted that date of conception may initially be difficult to determine. Subsequent study booking will be based on a derived date when late menstrual period dates, BHCG titre and/or ultrasound results are known. This is what would occur in standard clinical practice. Likely obstetric care provider will be recorded. Medical records including the results of the standard 75 g Oral Glucose Tolerance Test (26–28 weeks’ gestation), all ultrasonography reports and the Victorian Maternity Record will be obtained in all women.

If women elect to attend The Mercy Hospital and Royal Women’s Hospital for obstetric care, they will be asked to agree to an additional four study visits throughout pregnancy.Visit 3.1 (12 weeks pregnant): Maternal anthropometry and blood pressure will be measured (see Data and Biosample collection 1.1 and 1.2). A fasting maternal blood sample (20 ml) will be taken for measurement of plasma glucose, insulin, lipid profile (total cholesterol, LDL, HDL, triglycerides, non-esterified fatty acids (NEFA), leptin and C reactive protein (CRP).Visit 3.2 (26–28 weeks pregnant): Maternal weight, skin fold thickness measurements and blood pressure will be taken. Maternal bloods will be repeated as for Visit 3.1. A kit for maternal and cord blood collection (containing tubes and instructions) will be given to participants. This will be packed into the baby bag of subjects. This method of cord blood collection has been used successfully in the past.Visit 3.3 (Delivery): After the 3rd stage of labour, cord blood (20 ml) will be taken from the umbilical vein using direct puncture of the vessel with needle and syringe. Maternal blood will be taken (see Data and Biosample collection 1.1 and 1.2).Visit 3.4 (24-72 h post-delivery): Fetal anthropometry (see Data and Biosample collection 1.3) will be performed by one of two trained persons based on the protocol used in the HAPO study [57]. Maternal anthropometry and blood pressure will be performed (see Data and Biosample collection 1.1 and 1.2). Gestational weight gain will be calculated (to the nearest 0.1 kg).

All standard pregnancy care, including the decision to proceed with an early 75 g Oral Glucose Tolerance Test (OGTT), will occur at the discretion of the treating maternity team. If gestational diabetes is diagnosed at any gestation, treatment should proceed per usual local guidelines. The diagnosis of gestational diabetes will be documented in the participant file and all medical therapy used to manage gestational diabetes will be recorded. Given that these women will not have an OGTT at 26–28 weeks’ gestation, glucose samples from these participants cannot be used in the analysis of the primary outcome. Study samples should otherwise be collected per the study protocol (Fig. 1).

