**Methods/design:**

This study, a two-arm, parallel group, randomized control trial, will be conducted at the Metabolic Disorders Centre, University of Melbourne. This trial will recruit 164 women aged 18–38 years with a body mass index of 30–55 kg/m^2^ who plan to conceive in the next 6–12 months. Women will be randomized to one of two 12-week interventions (Group A and Group B). Group A will aim for modest weight loss (MWL; ≤ 3% body weight) using a hypocaloric diet. Group B will aim for substantial weight loss (SWL; 10–15% body weight) using a modified very low energy diet (VLED) program. All participants will be asked to comply with National Health and Medical Research Council (NHMRC) guidelines for exercise and will be provided with standard pre-pregnancy advice according to Royal Australian and New Zealand College of Obstetrics and Gynaecology guidelines. All participants will then be observed for the subsequent 12 months. If pregnancy occurs within the 12-month follow-up period, data on weight and metabolic status of the mother, and pregnancy outcomes of mother and offspring will be recorded.

The primary outcome is maternal fasting plasma glucose at 26–28 weeks’ gestation, given that this is known to correlate with pregnancy outcomes. Time to conception, live birth rate, gestational weight gain, and a composite of adverse pregnancy outcomes for mother and baby will comprise the secondary outcomes.

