### Aim

Primary aim: To determine if non-surgical substantial pre-conception weight loss (10–15% body weight) in obese (BMI ≥ 30 kg/m^2^) women causes a ≥ 10% reduction in fasting glucose at 26–28 weeks’ gestation when compared with modest pre-conception weight loss (≤ 3% body weight loss).

Secondary aims:

The secondary aims of the study are to determine if, in obese women (BMI ≥ 30 kg/m^2^), non-surgical substantial pre-conception weight loss (10–15% body weight) when compared with modest pre-conception weight loss (≤ 3% body weight), results in:A reduction in the composite end point of maternal gestational diabetes (IADPSG definition), LGA, intrauterine growth restriction (IUGR), gestational hypertension/pre-eclampsia, delivery before 37 weeks’ gestation, primary Cesarean section, shoulder dystocia/birth injury, neonatal hypoglycemia, neonatal hyperbilirubinemia, neonatal special care nursery, or intensive care admission.A reduction in the rate of maternal gestational diabetes (IADPSG definition).A reduction in the rate of LGA infants.A reduction in the rate of IUGR.A reduction in the rate of gestational hypertension/pre-eclampsia.A reduction in the rate of delivery before 37 weeks’ gestation.A reduction in the rate of primary Cesarean section.A reduction in the rate of birth injury/shoulder dystocia.A reduction in the rate of neonatal hypoglycemia.A reduction in the rate of neonatal hyperbilirubinemia.A reduction in that rate of neonatal special care nursery or intensive care admission.A reduction in maternal and neonatal length of stay.A decrease in the time to conception.An increase in live birth rate.No difference in maternal gestational weight gain.

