#### 1.1 Maternal anthropometry

Body weight will be measured (to the nearest 0.1 kg) using calibrated digital scales. Waist and hip circumferences will be measured (to the nearest 0.1 cm) using a standard tape measure according to the WHO guidelines (at the end of a normal expiration, at the midpoint between the lower margin of the last palpable rib and the top of the iliac crest, and around the widest portion of the buttocks, as the average of two measurements). Skin fold thickness measurement will occur according to the protocol published by Kannieappan and will involve triceps, biceps, subscapular skinfold thickness measurements plus arm circumference [59]. Measurements will be taken fortnightly during the weight loss phase (weeks 0–12), at week 16 and then 3 monthly for 12 months or until conception occurs. Post-conception measurements will occur at 12 and 26 weeks’ gestation and within 72 h of delivery.

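### Gestational weight gain has no named end weight; the study weights scheduled in pregnancy cannot give total gain, come from a self-selected visit subset, and cannot support a finding of no difference

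*Protocol article*

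**What the plan says.** All references are to the protocol article.

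- **Status.** The Abstract (Methods/design) lists the secondary outcomes as "Time to conception, live birth rate, gestational weight gain, and a composite of adverse pregnancy outcomes". The Aim section includes "No difference in maternal gestational weight gain" among the results that the trial is to determine.
- **Calculation.** Under Phase 3b: Pregnancy, the entry for Visit 3.4 ends with "Gestational weight gain will be calculated (to the nearest 0.1 kg". The entry is headed "Visit 3.4 (24-72 h post-delivery): Fetal anthropometry", and maternal anthropometry is done at the same visit. Neither the start weight nor the end weight of the gain is named.
- **Who has the visit.** Phase 3b sets the condition "If women elect to attend The Mercy Hospital and Royal Women’s Hospital for obstetric care", and then "they will be asked to agree to an additional four study visits throughout pregnancy".
- **Weights in pregnancy.** Section 1.1 Maternal anthropometry says "Post-conception measurements will occur at 12 and 26 weeks’ gestation and within 72 h of delivery". It does not repeat the two-hospital condition.
- **Records.** Phase 3b has the medical records and the state maternity record obtained for every pregnant woman. Outcome measures lists the secondary outcomes taken from the maternity record, and weight gain is not among them.
- **Analysis set.** Statistical analysis/Power calculation has secondary outcomes analysed in women who conceive and, where appropriate, by intention to treat. It gives no SD, margin or test for weight gain.

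**The concern.** The Background argues that a very low energy diet suits this setting partly because it can be stopped before conception, so that weight gain in pregnancy is left alone. It also links low gain to small babies. This secondary outcome is where the trial checks that argument.

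As written, the check has three weaknesses:

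1. The study schedule contains no weight from late pregnancy, so total gain cannot be formed from study weights.
2. The stated calculation belongs to a visit that only some pregnant women have. They enter that group by choices made after randomization (hospital, and consent to extra visits).
3. The aim is worded as an absence of difference, and a trial of this size could not show that through a non-significant result.

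At stake is a report that weight gain was unaffected, based on a quantity that is not gestational gain, in a subset, with an interval too wide to carry the statement.

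**Working it through.** **1. The plan's own figures.** The sample size section uses a difference of 6 and an SD of 10 at 80% power. Two-sided 5% is assumed, since alpha is not stated. Then n per arm = 2 × (1.96 + 0.842)² × (10/6)² = 43.6, so 44. The t-test version gives 44.6, so 45, as stated. Allowing for 45% without a live birth, 90 / 0.55 = 163.6, so 164, as stated. Thus 45 per arm is the planned number for the primary outcome, and 164 × 0.55 / 2 = 45.1 live births per arm. I use 45 as the best case for weight gain.

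**2. What the study weights can give.** Write G for total gain (weight just before delivery minus pre-conception weight), L for the mass lost at delivery, and P for the change from pre-conception to Visit 3.4.

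- *Post-delivery end weight:* P = G − L. Between arms (B = substantial, A = modest loss), P_B − P_A = (G_B − G_A) − (L_B − L_A). A loss common to both arms cancels; a difference in loss does not. Fewer large babies is a secondary aim, so L may differ by arm. If L is smaller in B, P_B − P_A lies above G_B − G_A, and a lower true gain in B would look smaller than it is. The documents give no figure for L_B − L_A, so I put no size on this.
- *26–28-week end weight:* for any birth at 37 weeks or later, at least 37 − 28 = 9 weeks of gain are missing.

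Neither equals G. The start weight is also loose: pre-conception visits are three-monthly, so the last one may be up to about three months before conception.

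**3. Who is measured.** Analysis set in the statistics section: women who conceive. Set with the stated calculation: women who conceive, choose either of two hospitals, and agree to four extra visits. The share is not given, so it is treated as a range below.

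**4. Precision.** The SD of weight gain is not given; 5 to 8 kg is assumed. The 95% CI half-width = 1.96 × SD × √(2/n).

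| Share measured | n per arm | SD 5 kg | SD 6.5 kg | SD 8 kg |
|---|---|---|---|---|
| all | 45 | 2.1 | 2.7 | 3.3 |
| 75% | 33.75 | 2.4 | 3.1 | 3.8 |
| 50% | 22.5 | 2.9 | 3.8 | 4.7 |
| 25% | 11.25 | 4.1 | 5.4 | 6.6 |

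With the t multiplier 1.99, the first row runs from 2.1 to 3.4 kg.

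**5. What a non-significant result would mean.** Chance of p > 0.05 over SD 5–8 kg (normal approximation):

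| True difference | 45 per arm | 22.5 per arm |
|---|---|---|
| 2 kg | 52–78% | 73–87% |
| 3 kg | 19–57% | 48–76% |

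**6. What equivalence would need.** Two one-sided 5% tests, true difference zero, 80% power: smallest margin = (1.645 + 1.282) × SD × √(2/n). With 45 per arm this is 3.1–4.9 kg; with 22.5 per arm it is 4.4–7.0 kg.

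**The case against.** The strongest reply has five parts.

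- **The end weight is an inference.** A reader might infer that the plan defines gain as post-delivery minus pre-pregnancy weight. The text says only that gain is calculated at Visit 3.4, which is also when the pregnancy data are complete. That stands, so mistimed measurement is not a stated fact. But the only other late study weight is at 26–28 weeks, so the point does not depend on which one was meant.
- **A common loss at delivery cancels.** Assuming a loss of 4–6 kg, a 9 kg gain would be recorded as 3–5 kg, and a reader might conclude that women would be misclassified against the 5 kg threshold in the Background. That threshold is background from a cited study; no outcome in this trial classifies women by it. Only a between-arm difference in the loss biases the comparison, and it cannot be sized from the document.
- **No faulty test is stated.** A reader might infer that equality is to be declared from lack of significance, or count the missing equivalence margin as an omission. The article states no test or decision rule for this outcome, a margin belongs in an analysis plan that is not shown, and the Discussion speaks only of exploring weight gain. What remains is the wording of the aim.
- **The aim is not impossible.** A subset lowers precision and may bias, but the arms can still be compared. Section 1.1 lists the pregnancy weights without the hospital condition, although the visits that provide them carry it in Phase 3b.
- **The maternity record may already hold late weights.** It may, but the article does not say so and does not list weight gain among the outcomes taken from it.

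**Conclusion.** The point holds in limited form. The article names neither end of the weight gain, and no scheduled study weight yields total gestational gain. Its only stated calculation belongs to a self-selected, post-randomization subset that does not match the analysis set of women who conceive. The comparison remains possible, but on a different quantity, with possible selection bias and reduced precision.

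At the best-case 45 per arm, the half-width of about 2.1–3.3 kg (up to 3.4 kg with the t multiplier) is too wide for a non-significant result to establish an absence of difference, and measuring half widens it to 2.9–4.7 kg. These figures rest on the assumed SD of 5–8 kg, the assumed share measured and a two-sided 5% level. The document does not support saying that the aim is unattainable or that a wrong test is planned. The primary outcome is not affected.

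**What to change.** 1. **Define the outcome.** Gain = last recorded antenatal weight minus last pre-conception study weight, accounting for gestational age at the antenatal weight (per week of gestation, or by adjustment).
2. **Name the source.** Take the antenatal weight, where recorded, from the maternity and medical records already obtained for all pregnant women. Report by arm how many have one and at what gestation.
3. **Relabel Visit 3.4.** Report that figure separately as early postpartum weight change in women who had the visit.
4. **Keep the 26–28-week study weight for a sensitivity analysis.** It comes from the same two-hospital visits, so it cannot replace missing weights in other women.
5. **Reword the aim.** Estimate the between-arm difference with its 95% CI, and claim no equivalence unless a margin is pre-specified. The margins in step 6 of the working show what the trial could support.

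Cost: wording, plus extraction of one weight and its date from records already requested. The downside is weights from clinic scales at variable times. That the records hold late-pregnancy weights is an assumption to check on a sample first.

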**Fig. 1 Fig1:**
[figure not shown]
*Flow chart* of study protocol

### Outcome measures

The results of the standard 75 g oral glucose tolerance test (OGTT) performed at 26–28 weeks’ gestation will be collected in all participants (except those who had an early OGTT which was positive; these subjects will not have a OGTT at 26–28 weeks’ gestation and therefore these subjects are excluded from the primary outcome). The fasting maternal plasma glucose from the 75 g Oral Glucose Tolerance Test performed at 26–28 weeks’ gestation will be used for analysis of the primary outcome. This test is part of standard maternity care and the sample could be taken in any one of the pathology collection centres across Victoria. Storage and processing of samples will occur according to the standard protocol of the pathology company. While it is acknowledged that samples may be processed in different laboratories using different techniques (hexokinase method or glucose oxidase method), it is anticipated that using this sample as the primary outcome will maximise the number of samples available for analysis. If samples are taken, stored and processed according to the standard protocol of the pathology company, the inter-assay variation is likely to be extremely low [58].

All women who agree to take part in the study throughout pregnancy will also have fasting glucose samples taken at their scheduled 26–28 weeks’ gestation study visit. This glucose sample will not be taken on the same day as the 75 g OGTT but will be taken during the same 26–28 week gestation window. This sample will be taken after an 8–12 h fast and between 08:00 and 10:00 am. Samples will be stored and batch tested as per Methodology 1.4. Analysis of these glucose samples will occur by the hexokinase method. These results will be compared to the fasting maternal plasma glucose samples from the 75 g Oral Glucose Tolerance Test. These samples will be used to validate the glucose results that comprise the primary outcome.

After delivery, the Victorian Maternity record will be obtained in all women who become pregnant. This will provide data on secondary outcomes including large-for gestational age, pre-eclampsia, small for gestational age (SGA), delivery before 37 weeks’ gestation, caesarean section, shoulder dystocia/birth injury, neonatal hypoglycemia, neonatal hyperbilirubinemia, and special care nursery or neonatal intensive care admission.

